### Randomisation and blinding

Randomisation will be achieved by means of a Web-based system created by the Peninsula Clinical Trials Unit in conjunction with the study statistician. The participants will be allocated to the protective socks intervention or to standard care in equal proportions, using blocks of fixed size to generate the allocation sequence and achieve balance in the numbers of participants allocated to each group. Variable block sizes were considered but would provide no advantage since the number of participants recruited at each care home is likely to be small. Randomisation will be stratified by geographical area (i.e. Exeter, Exmouth/Sidmouth and Mid Devon).

The Web-based randomisation system created and maintained by the clinical trials unit will allow secure access via computers or other devices with Internet connectivity. Research nurses will be provided with log-in details and will perform randomisation from the care home by smart phone. The system ensures allocation is concealed prior to performing randomisation. Telephone randomisation will be available during working hours (09:00 to 17:00, Monday to Friday inclusive) in the unlikely event the Web-based service is unavailable.

Blinding will not be possible for participants or research nurses. Blinding is possible for the data analyst, however, by coding the group allocation in the data file.

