The participants will be recruited primarily from Care Quality Commission registered care homes. Residents of care homes are widely recognised to be an under-researched population and at high risk of suffering skin tears. Depending on recruitment rate of both homes and participants, up to 45 homes are expected to take part. In order to augment recruitment, patients in the community will also be invited to participate. For logistical reasons, in order to maximise efficiency in terms of research nurse resource, recruitment efforts will be focused on three geographical areas successively (Exeter, Exmouth/Sidmouth and Mid Devon, roughly representing urban, coastal and rural situations, respectively).

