### Sample size

The target sample size for this pilot trial is 90 participants. The sample size was based on a group sample of 40 with a 20% inflation to allow for dropout and loss to follow-up. A sample of 40 in each group was considered to be adequate for providing robust estimates of skin tear incidence, skin tear-free days and standard deviations for quality of life and other outcome measures.

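### Variable block sizes are rejected because few people are recruited per care home, but the blocks run within three areas and not within homes, so the reason does not apply

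*Protocol article*

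**What the plan says.** All of the randomisation scheme is in the section Randomisation and blinding of the protocol article. Allocation is 1:1, "using blocks of fixed size to generate the allocation sequence and achieve balance in the numbers of participants allocated to each group". The next sentence gives the reason for not varying the size: a variable size "would provide no advantage since the number of participants recruited at each care home is likely to be small". The stratification follows: "Randomisation will be stratified by geographical area (i.e. Exeter, Exmouth/Sidmouth and Mid Devon". No blocking or stratification by care home is described.

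The same section has research nurses carry out the randomisation themselves by smart phone, says that the web system hides each allocation until it is issued, and adds: "Blinding will not be possible for participants or research nurses".

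Other sections supply the setting:

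- Method/design: "recruitment efforts will be focused on three geographical areas successively", to save research nurse time, with up to 45 homes.
- Informed consent: the research nurse judges capacity and takes consent. Table 2 makes capacity, as judged by that nurse, an eligibility criterion.
- Recruitment of patients from the community: these participants need not live in any care home.
- Sample size: "The target sample size for this pilot trial is 90 participants".

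**The concern.** The choice between fixed and variable block sizes turns on how long a sequence a recruiter can observe. Small numbers per home would settle it only if each home had its own sequence. Here one sequence serves a whole area, so a nurse moving from home to home keeps seeing the same list.

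Web concealment stops anyone reading the next entry. It does not stop someone from working it out once the rest of a fixed block has been seen. The person who could do so also decides whether a resident has capacity and can influence who is enrolled next. If that discretion were used, the people entering the two groups could differ. The by-group descriptions of skin tear-free days, incidence and severity would then be harder to interpret, and a mistaken rationale could pass into the definitive trial.

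**Working it through.** **Inputs.** From the article: 1:1 allocation, fixed blocks of unstated size, three area strata, 90 participants, up to 45 homes. Assumed: equal areas, so 90/3 = 30 per sequence; and, for the per-home check only, all 90 participants spread over 45 homes, so 90/45 = 2 per home. There is no figure in the plan to reproduce on this point.

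**Step 1: does the stated reason work for the scheme it implies?** Suppose blocks did run within homes, with two participants each. In a block of 4 an allocation can be certain only from the third position on, and in a block of 6 only from the fourth. With two people per home, 0% of allocations are certain, whether the size is fixed at 4 or 6 or varies between them. So at these sizes the reason is sound for blocks within homes, which is not the scheme described.

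**Step 2: blocks within areas, size known, whole sequence seen.** In a complete block of size k, the certain allocations are the final run of one arm. Its expected length is k/(k/2 + 1), so the expected share is 1/(k/2 + 1). The table also gives the result of simulating 6,000 sequences of 30 per area with an optimal guesser. Chance guessing is 50%.

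| Fixed size | 1/(k/2 + 1) | Certain, 30 per area | Of 90 | Correct guesses |
|---|---|---|---|---|
| 2 | 50% | 50.0% | 45 | 75% |
| 4 | 33% | 31.1% | 28 | 70% |
| 6 | 25% | 24.9% | 22 | 68% |
| 8 | 20% | 16.6% | 15 | 65% |
| 10 | 17% | 16.8% | 15 | 65% |

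At sizes 4 and 8 the simulated share is lower because 30 is not a multiple of the size and the last block is incomplete. For size 4: 7 complete blocks × 4/3 = 9.33 per area, and 3 × 9.33 = 28.

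**Step 3: size fixed but unknown to the guesser, who considers 2, 4, 6 or 8.**

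| True size | Certain | At least 90% confident | Correct guesses |
|---|---|---|---|
| 2 | 3.3% | 33.3% | 75% |
| 4 | 8.1% | 24.1% | 70% |
| 6 | 14.4% | 21.2% | 68% |
| 8 | 13.3% | 18.3% | 65% |

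Withholding the size removes most of the strict certainty. Near-certain predictions remain, because a fixed size can be learned from the sequence.

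**Step 4: sizes varying at random within area, set of sizes known to the guesser.**

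| Sizes | Certain | Of 90 | At least 90% confident | Correct guesses |
|---|---|---|---|---|
| 2, 4 | 10.7% | 10 | 17.3% | 72.0% |
| 4, 6 | 5.7% | 5 | 8.9% | 68.7% |
| 2, 4, 6 | 3.8% | 3 | 6.4% | 69.9% |
| 4, 6, 8 | 2.4% | 2 | 4.6% | 67.5% |

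Against a known fixed size of 4, sizes 4 and 6 cut certain allocations from about 28 to about 5 of 90. The correct-guess rate hardly moves: 68.7%, against 70.0% for fixed 4 and 68.4% for fixed 6.

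**The case against.** The strongest reply is that much of the apparent size rests on what the article does not say.

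- **A reader might infer that about 30 of the 90 allocations were known in advance.** That needs a block size of 4, nurses who know it, and every allocation in an area seen by one nurse or shared among all. None of these is stated. An article may leave the block size, and steps to keep it from the nurses, to the full protocol, so their absence is no fault and cannot support a worst case.
- **A reader might infer one small nurse team across all areas.** The article says only that areas are taken in turn to save nurse time. It does not give the number of nurses or say whether they see each other's allocations.
- **A reader might extend the point to recruitment rates by arm or to the grading of injuries.** Recruitment precedes allocation, so it has no rate by arm. Grading by unblinded nurses is a matter of detection bias, which block size does not affect, and a blinded specialist reviews the photographs.
- **A reader might fear a biased treatment effect.** Under Statistical methods the pilot describes outcomes in each group and leaves the intention-to-treat comparison to the definitive trial.
- **Nurse discretion is limited.** Care home staff identify potential residents, community candidates come from record or database searches, with doctor screening at practices, and consent and baseline measures come before randomisation.

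These points stand and limit the size. They do not repair the stated reason, which speaks of homes when the strata are areas. Some discretion also remains, since the nurse judges capacity and approaches residents before consent.

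**Conclusion.** The stated reason for keeping fixed blocks does not fit the design, and the claim of no advantage is wrong as written. How far this exposes the trial depends on facts not given. With the size known and the whole area sequence seen, certain allocations range from 50% at size 2 to about 17% at size 10. With the size unknown, strict certainty is about 3-14%, although predictions held with at least 90% confidence still cover 18-33%. These figures assume 30 participants per area and full sight of each area's sequence; a nurse who sees only part of it would predict less.

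Nothing in the article suggests that anyone predicted or steered allocations. This is an inexpensive improvement to the design. What is at risk is the by-group descriptive figures of the pilot and the procedure handed on to the definitive trial, not an effectiveness test here.

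**What to change.** Delete the statement that variable block sizes would bring no advantage. Use randomly varying block sizes within each area, and state that the sizes are withheld from the research nurses. Withholding matters because varying the size lowers certainty far more than it lowers the overall guess rate.

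Apply this to any list not yet used, and in the definitive trial. Trial status calls recruitment ongoing but schedules its end for October 2014, before the April 2015 publication. Little or no list may remain, and the main use is then in the definitive trial.

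The cost is a setting in the web randomisation system. The downside is a possible imbalance at the end of each stratum of at most half the largest block: 6/2 = 3 people per area with sizes 4 and 6, against 4/2 = 2 with a fixed size of 4.

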### Sample size

The target sample size for this pilot trial is 90 participants. The sample size was based on a group sample of 40 with a 20% inflation to allow for dropout and loss to follow-up. A sample of 40 in each group was considered to be adequate for providing robust estimates of skin tear incidence, skin tear-free days and standard deviations for quality of life and other outcome measures.

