**Methods/design:**

In this pilot parallel group, randomised controlled trial, 90 people at risk of skin-tear injury will be randomised with equal allocation to receive the intervention or usual care. They will be recruited from care homes and from the community via general practices and a research volunteer database. Pilot outcomes include recruitment, eligibility, attrition, ascertainment of injuries and completion of outcome measures. Acceptability of the intervention and of study participation will be explored using semi-structured interviews. The proposed primary outcome for the future definitive trial is skin tear-free days. Secondary outcomes are skin tear severity, health status, specific skin-tears quality of life, capability and fear of falling, measured at baseline and the end of the study and in the event of a skin tear.

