## Method/design

The study is an open, parallel group, randomised controlled study in which participants are randomised to one of two groups; the intervention group will wear the protective socks on a daily basis for a period of 16 weeks whilst the participants in the control group will wear their usual clothing. See Figure 1 for the patient flow diagram and Table 1 for the study schedule. The study is conducted in Devon, UK and aims to recruit 90 participants, 45 in each arm. The main eligibility criteria for participants are presented in Table 2. Experiences of using the socks and/or taking part in the study will be captured through semi-structured interviews with a purposive sample of participants from both the intervention and control arms of the study.

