### Statistical methods

The study will be analysed using the statistical package SPSS v. 20 (IBM Corp, New York). Missing data will be investigated and the proportion missing will be recorded but are expected to be minimal. Multiple imputation methods or any specific imputation methods recommended by the authors of the questionnaire will be used to obtain realistic estimates of scores for future planning of questionnaire usefulness. All the questionnaires concerning acceptability of the socks will be scored and summarised using appropriate measures of central tendency and dispersion. Data on lacerations will also be summarised in a similar way. Agreement on wound grading between research nurses and a blinded tissue viability expert (AK) will be assessed from anonymised photographs using weighted kappa. Numbers of eligible residents, recruitment, attrition and loss to follow-up (as per the Consolidated Standards of Reporting Trials (CONSORT) diagram) will be reported as proportions, confidence intervals will be reported wherever appropriate. The main analysis will describe skin tear-free days and the incidence and severity of skin lacerations in each group.

The pilot study will determine the feasibility of how the outcomes can be measured. These will be used to inform the sample size of the full-scale randomised controlled trial. In that trial, we intend to compare the incidence of skin damage between the two groups on an intention-to-treat basis and the size of any wounds by objective assessors (research nurses). The clustering effects of homes will be an issue in the analysis of a future definitive randomised controlled trial, and sample size inflation will need to be considered for a mixed effects model with “homes” as a random effect.

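### The target of 45 per group does not follow from 40 per group with a 20% inflation, which gives 48 or 50

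*Protocol article*

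**What the plan says.** The Sample size section of the protocol article opens with the total: "The target sample size for this pilot trial is 90 participants". It then gives the derivation: "The sample size was based on a group sample of 40 with a 20% inflation to allow for dropout and loss to follow-up". The reason for choosing 40 follows: "A sample of 40 in each group was considered to be adequate for providing robust estimates of skin tear incidence, skin tear-free days", and the same sentence extends this to the standard deviations of the quality-of-life and other measures.

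The split between arms is stated elsewhere. The abstract has "90 people at risk of skin-tear injury will be randomised with equal allocation to receive the intervention or usual care", and the Method/design section says the study "aims to recruit 90 participants, 45 in each arm".

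The base (40 per group), the allowance (20%) and the result (45 per group, 90 in total) are therefore all explicit. No other section gives a different dropout rate or explains the step from 40 to 45.

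**The concern.** A base number, an inflation and a total are given, and the total cannot be obtained from the other two. This is a disagreement between stated figures, not a detail left to a fuller document.

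The 40 per group is the only justification offered for the pilot's size. The Trial objectives and Statistical methods sections say the pilot's estimates will inform the sample size of the definitive trial. Attrition is both a specific objective and a listed pilot outcome, so readers will compare the observed loss with the allowance stated here. Someone who takes the section at face value would believe that 45 per group absorbs the full 20% allowance and still leaves 40. It does not, whichever way the 20% is read.

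**Working it through.** **Inputs, all from the protocol article**
- Base: 40 per group (Sample size).
- Allowance: 20% (Sample size).
- Target: 90 in total (Sample size), 45 per arm (Method/design), equal allocation (abstract).

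**Step 1: try to reproduce the plan's figure**
- 20% as an add-on, n × (1 + d): 40 × 1.20 = 48 per group, 96 in total.
- 20% as a loss rate, n / (1 − d): 40 / 0.80 = 50 per group, 100 in total.

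Neither gives 45 per group or 90 in total.

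**Step 2: work back from 45**
- Inflation applied: 45/40 − 1 = 12.5%.
- Largest loss that still leaves 40: 1 − 40/45 = 11.1%.

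**Step 3: look for another route to 90**
- A 10% loss rate: 40 / 0.90 = 44.4, rounded up to 45 per group, 90 in total. This matches the target, but the stated figure is 20%.
- Adding 20% of one group to the total of both: 80 + 8 = 88. This is near 90, but it is not an inflation of each group.

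**Step 4: what 45 per group would leave**
- If 20% is the loss rate: 45 × 0.80 = 36 per group, 72 in total.
- If 20% is an add-on, 48 per group implies a tolerable loss of 1 − 40/48 = 16.7%. At that loss, 45 × (40/48) = 37.5 per group.

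Both are below 40.

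**Step 5: effect on precision, 40 against 36 per group**

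For a standard deviation, the 95% limits are the estimate times √[(n−1)/χ²], using the 0.975 and 0.025 quantiles on n−1 degrees of freedom:
- n = 40: 0.82 to 1.28.
- n = 36: 0.81 to 1.30.

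For incidence, the approximate 95% half-width is 1.96 × √[p(1−p)/n]. The article gives no expected 16-week incidence, so p is an assumption and a range is shown:

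| Assumed p | n = 40 | n = 36 |
|---|---|---|
| 14% | 10.8 points | 11.3 points |
| 20% | 12.4 points | 13.1 points |
| 50% | 15.5 points | 16.3 points |

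The difference is below one percentage point throughout.

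**The case against.** The strongest reply is that little depends on the error. This is a feasibility pilot with a descriptive main analysis and no power calculation. The 40 was a judgement of adequacy, not a computed threshold, and the intervals hardly move between 40 and 36. That stands, and it limits the severity.

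A second reply is that the slip may lie in the percentage. A 10% loss rate leads exactly to 45 per group, in which case 40 would be retained at the planned loss and only the 20% would be wrong. The article cannot settle which figure is the mistake. This also stands.

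Two stronger readings are tempting, and the document does not support either.

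- A reader might infer that the pilot will end with 36 per group. The text speaks of an inflation of 20% and does not say that 20% loss is expected, so 36 holds only if the 20% is read as a loss rate. Even then it applies to complete 16-week data. Under Withdrawal and dropout, data gathered before withdrawal stay in the analysis unless the participant asks for their removal, and people who stop wearing the socks may still complete outcome measures. Baseline scores and their standard deviations can draw on all 45 per arm.
- A reader might also see a conflict with the Statistical methods section: "Missing data will be investigated and the proportion missing will be recorded but are expected to be minimal". That sentence leads straight into imputation methods, including those recommended by the questionnaire authors, for obtaining realistic scores. Attrition and loss to follow-up are reported separately in the same section, and the list of pilot outcomes also separates attrition from questionnaire completeness. Expecting few missing values in collected data is compatible with allowing for dropout.

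None of this explains how 40 and 20% give 45.

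**Conclusion.** The inconsistency is real but minor. As written, the stated basis gives 48 per group (96 in total) or 50 per group (100 in total), not 45 (90 in total). The target is short by 3 or 5 participants per group relative to its own derivation. It corresponds to a 12.5% inflation and leaves 40 per group only if loss does not exceed about 11%.

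The arithmetic rests only on the article's figures and equal allocation. The consequence of about 36 per group rests on two further conditions: that 20% is the loss rate, and that only participants with complete 16-week data are counted. Under those conditions the number is 10% below 40 (4/40), and precision is only slightly worse. No design decision in the pilot depends on it.

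**What to change.** Keep 90 and restate the basis in the Sample size section in one of two ways:

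- 45 per group allows for about 11% loss, to leave 40 per group; or
- 45 per group with 20% loss leaves about 36 per group with complete follow-up.

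Under the second option, the statement that 40 per group is adequate should be reworded to refer to about 36. The choice depends on which figure the investigators intended, and they should say so.

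The Statistical methods sentence on missing data should stay as it is.

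The cost is one or two reworded sentences. Recruitment, conduct and analysis are unaffected. The only price is that the stated allowance, or the stated retained number, becomes somewhat less favourable.

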**Figure 1 Fig1:**
[figure not shown]
Participant pathway diagram (taken from the Participant Information Sheet).

**Table 1 Tab1:** Tabulated study schedule

Study procedure	Set up (Visit 1)	Baseline/Study Day 0 (Visit 2)	Study Day 1 (the day after consent)	Upon new injury	Weekly* for 16 weeks	Study Day 112	Qualitative data collection
Identify potentially eligible participants	X						
Provide Participant Information Sheet	X						
Informed consent		X					
Collection of baseline information		X					
EQ5D-5 L questionnaire		X		X^c^		X	
ICECAP-O questionnaire		X		X^c^		X	
FES-I (short) questionnaire		X		X^c^		X	
Randomisation		X					
Provision of socks (intervention arm only)		X					
Wearing of socks (intervention arm only)			X --------------------------------- > X				
Completion of participant diary (intervention arm only)			X --------------------------------- > X				
Photograph wound				X^b^			
Measurement of wound				X^b^			
Wound scoring				X^b^			
Cardiff wound impact schedule^a^				X^c^		X^d^	
Adverse event recording			X --------------------------------- > X^e^				
Research nurse to visit care home for progress checks					X		
Patient interviews							X
Focus groups							X

^*^Regular contact (visit or telephone), approximately weekly.

^a^Completed only by participants who experienced one or more skin tear injuries during their study participation.

^b^Performed within one working day following injury.

^c^Performed seven days post-injury.

^d^Completed on Day 112 by all participants who experienced skin tear injury during the study. In addition, participants who incur an injury during week 16 (Day 106 to 112 inclusive), will also complete the questionnaire seven days post-injury.

^e^Day 112 or Day 112 + 1 to 7 days if a skin tear injury occurs during week 16.

**Table 2 Tab2:** Main eligibility criteria (inclusion and exclusion criteria)

Inclusion criteria	Exclusion criteria
Resident in a care home or living in the community and at high risk of skin tears.	Not competent to give informed consent in the opinion of the recruiting nurse.
Aged 65 years or older.	Bedbound.
Ambulatory and/or wheelchair user able to take part in daily activities within a care home or in the community.	Being treated for current lacerations or ulcers on their legs.
	Participant likely to use graduated compression stockings or similar during the intervention period.

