Specific objectives of this pilot study are therefore:To examine the feasibility and acceptability of the research design, methods and outcome measures prior to a definitive randomised trial.To assess the processes for capturing outcome data.To refine the intervention if appropriate through qualitative work on acceptability.To determine recruitment and retention rates (at care home and resident or community participant level) to a randomised trial.To estimate concordance with the intervention.To estimate attrition rates from the study.To consider outcome measures which are important and appropriate for participants for use in the full trial.To evaluate the appropriateness of two systems of skin tear classification as outcome measures for the main trial.To estimate rates of questionnaire completion.To obtain baseline estimates of scores on the proposed outcome measures in this clinical population.To estimate the variability of outcomes to inform the sample size of the definitive trial.To calculate the sample size required for a definitive trial.To help establish the eligibility criteria for the future definitive trial (primary care patients, care homes and residents).To estimate the ability to obtain cost and effectiveness measures.To refine the clinical protocol for the use of protective socks in the full trial.To gain further understanding of the practicalities of running a trial in this population.To obtain feedback from nursing homes regarding the acceptability of the study.

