#### Other secondary outcome measures

Standardised measure of health status (EQ-5D-5L): collected at baseline, 16 weeks and in the event of a skin tear injury.Assessment of capability (ICECAP-O): collected at baseline, 16 weeks and in the event of a skin tear injury.Assessment of fear of falling (Short FES-I): Collected at baseline, 16 weeks and in the event of a skin tear injury.Disease-specific quality of life measured by Cardiff Wound Impact Schedule: Collected in the event of a skin tear injury and at 16 weeks (from participants who have had a skin tear).Adverse events caused by the socks.Health care resource use: collected in the event of a skin tear injury.Outcome measures for the pilot study are:Recruitment rate for homes.Proportion of participants (home residents) eligible.Recruitment rate for participants.Attrition and loss to follow up.Ascertainment of injuries.Completion and completeness of study questionnaires.Estimates of the distribution of outcome measures.Feasibility of the workload.Acceptability of the intervention to participants.Acceptability of study participation to participants.

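### The 40-per-group adequacy claim does not hold for the Cardiff Wound Impact Schedule, wound size or skin tear grade, which are collected only from injured participants

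*Protocol article*

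**What the plan says.** The Sample size section sets the total: "The target sample size for this pilot trial is 90 participants". It explains the figure: "The sample size was based on a group sample of 40 with a 20% inflation to allow for dropout and loss to follow-up". It then calls 40 in each group "adequate for providing robust estimates of skin tear incidence, skin tear-free days and standard deviations for quality of life and other outcome measures".

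Elsewhere the article says who supplies each measure:

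- **Everyone.** EQ-5D-5L, ICECAP-O and Short FES-I are taken at baseline and at 16 weeks (Table 1; Other secondary outcome measures). Incidence and tear-free days are also defined for every participant (Primary outcome).
- **Injured participants only.** The footnote in Table 1 on the Cardiff Wound Impact Schedule reads "Completed only by participants who experienced one or more skin tear injuries during their study participation". The list under Other secondary outcome measures agrees. Wound size and the Payne-Martin and STAR grades are recorded at the visit that follows an injury (Procedure in the event of a skin tear injury).

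The abstract's list of secondary outcomes begins with skin tear severity and goes on to "specific skin-tears quality of life, capability and fear of falling, measured at baseline and the end of the study". Table 1 has no baseline mark for the Cardiff schedule or for wound scoring.

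**The concern.** A participant who has no tear has no Cardiff score, wound size or grade, by design. For these measures the number analysed is the number injured, and that must be smaller than the group unless everyone has a tear. The adequacy statement draws no such distinction.

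This matters because the Trial objectives use the pilot to estimate outcome variability for the definitive trial and to judge two skin tear classifications as outcomes for it. The Outcome measures section also places severity within the future primary focus. A reader who relies on the Sample size section could treat a standard deviation from a few injured people as if it came from 40 per group.

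The abstract's timing is a related slip. Participants enter with no unhealed tear (Primary outcome), and people under treatment for current leg lacerations or ulcers are excluded (Table 2). A tear-specific score at baseline has nothing to refer to.

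**Working it through.** **The plan's own figure.** The inputs are 40 per group and 20% inflation (Sample size). Dividing gives 40/(1 − 0.20) = 50 per group, 100 in total. Multiplying gives 40 × 1.20 = 48 per group, 96 in total. Neither gives 90. The planned 45 per arm is 45/40 − 1 = 12.5% inflation. That is a separate matter, and nothing below depends on it. I take the plan's 40 per group as given.

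**Expected number injured per 40.** All rates come from the Background; follow-up is 112 days (Primary outcome).

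- Lowest cited incidence, 2.23%: 40 × 0.0223 = 0.9.
- Highest cited incidence, 41.5%: 40 × 0.415 = 16.6.
- 14% of nursing home residents per month, treated as a constant and independent monthly risk: 112/30.44 = 3.68 months; 1 − 0.86^3.68 = 0.426; 40 × 0.426 = 17.0.

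The range is therefore about 1 to 17. The 2.23% and 41.5% figures are given without a time window or body site, so applying them to 16 weeks is an assumption.

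**Is 17 a ceiling?** No. With all 45 per arm retained, the monthly rate gives 45 × 0.426 = 19.2. With 40 per arm and a risk of 0.426, the binomial probability of more than 17 injured is about 0.44.

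**Is 17 likely to be low or high?** Probably high. The cited rates are not limited to leg tears, and the Background says arm injuries are more common. The trial also takes community participants. If half of tears were on the leg (assumption), 40 × 0.415 × 0.5 = 8.3, or about 8 per arm.

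**Precision of a variance pooled over the two arms.** With n per arm, df = 2n − 2. The 95% upper limit as a multiple of the estimate is df/χ²(0.025; df), assuming normal data and a common variance.

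| n per arm | df | χ²(0.025) | Variance upper limit | SD upper limit |
|---|---|---|---|---|
| 40 | 78 | 55.47 | 1.41 | 1.19 |
| 17 | 32 | 18.29 | 1.75 | 1.32 |
| 8 | 14 | 5.63 | 2.49 | 1.58 |

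With 1 injured per arm, df = 0 and no pooled variance can be estimated. For a continuous outcome the required sample size is proportional to the variance, so the variance column is also the factor by which a definitive trial sized on the point estimate could fall short.

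**The case against.** The strongest reply is that the sentence is sound for most of what it covers. Incidence, tear-free days and the three generic questionnaires are measured in everyone, and the injured-only rule for the Cardiff schedule is stated openly. A careful reader of the whole article would not take its sample size to be 40. Nor does the article say that the definitive trial will be sized on the Cardiff standard deviation: the proposed primary outcome is tear-free days, and QALYs come from EQ-5D-5L. All of this stands, and it keeps the point minor. It does not make the unqualified statement correct for the measures it does not fit.

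A reader might also infer more than the documents support:

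- **That 17 per group is the best case.** It is an expected count under a borrowed rate, and it can be exceeded.
- **That the loss of precision should be read arm by arm.** Single-arm variance limits are larger (2.3-fold at 17, 4.1-fold at 8), but a pooled standard deviation is the natural planning quantity, so the pooled figures are the fair ones.
- **That the weighted kappa is affected in the same way.** Agreement is assessed on wound photographs. Its unit is the wound, over both arms and with repeat tears, and the Sample size section claims nothing about it.
- **That scores would be imputed for uninjured people.** Statistical methods proposes no such thing.
- **That the objective "To obtain baseline estimates of scores on the proposed outcome measures in this clinical population" promises a baseline wound score.** It is a general aim, and the Trial objectives text ties baseline scores to the quality of life questionnaires.

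**Conclusion.** The point holds as a minor one. The Sample size section credits the design with a precision that it does not deliver for the Cardiff Wound Impact Schedule, wound size and skin tear grade. Their basis is about 1 to 17 expected injured participants per 40. The pooled variance upper limit then rises from 1.41 times the estimate to about 1.75 times at 17 per arm and 2.5 times at 8. These sizes rest on the cited background rates carrying over to 16 weeks in this population, on a constant independent monthly risk for the 14% figure, and on normal data for the chi-square limits. The figure of 8 per arm rests on an assumed share of leg tears.

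The structural finding needs none of these assumptions: whatever the injury rate, these measures exist only for the injured. The abstract's baseline timing likewise contradicts Table 1 at any rate. The adequacy statement is not challenged here for measures taken on all participants.

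**What to change.** 1. In the Sample size section, limit the 40-per-group statement to incidence, tear-free days, EQ-5D-5L, ICECAP-O and Short FES-I.
2. Add that the Cardiff schedule, wound size and grade rest on injured participants only, with about 1 to 17 expected per 40 under the cited rates, labelled as an assumption-based range.
3. Report the standard deviations of these measures pooled over arms with confidence intervals, and do not use them as point values to size the definitive trial.
4. Correct the abstract so that no baseline measurement is claimed for skin tear severity or skin-tear-specific quality of life.

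The cost is wording and reporting, with no added participants or data. The downside is that the stated precision for the wound-specific measures becomes less favourable.
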